## Abstract

**Background:**

According to the Word Health Organization, patients who can benefit from palliative care should be identified earlier to enable proactive palliative care. Up to now, this is not common practice and has hardly been addressed in scientific literature. Still, palliative care is limited to the terminal phase and restricted to patients with cancer. Therefore, we trained general practitioners (GPs) in identifying palliative patients in an earlier phase of their disease trajectory and in delivering structured proactive palliative care. The aim of our study is to determine if this training, in combination with consulting an expert in palliative care regarding each palliative patient's tailored care plan, can improve different aspects of the quality of the remaining life of patients with severe chronic diseases such as chronic obstructive pulmonary disease, congestive heart failure and cancer.

**Methods/Design:**

A two-armed randomized controlled trial was performed. As outcome variables we studied: place of death, number of hospital admissions and number of GP out of hours contacts.

**Discussion:**

We expect that this study will increase the number of identified palliative care patients and improve different aspects of quality of palliative care. This is of importance to improve palliative care for patients with COPD, CHF and cancer and their informal caregivers, and to empower the GP. The study protocol is described and possible strengths and weaknesses and possible consequences have been outlined.

**Trial Registration:**

The Netherlands National Trial Register: NTR2815

## Background

According to the World Health Organization (WHO) palliative care is 'an approach that improves the quality of life of patients and their families facing the problems associated with life-threatening illness, through the prevention and relief of suffering by means of early identification and impeccable assessment and treatment of pain and other problems, physical, psychosocial and spiritual' [1]. A first challenge evoked by this definition is the early identification of a patient who may benefit from palliative care. Although the WHO-recommendations have been accepted worldwide, no scientific papers have been published yet on how to identify patients who could potentially benefit from an earlier start of a palliative care in general practice. A literature review of Qaseem et al. did not identify any validated tools that predict the optimal timing to initiate palliative care services in general practice,[2] despite the fact that a lot of research has been undertaken to elucidate the prediction of mortality, survival, and prognostication for patients with advanced cancer and non-cancer diseases [3-10]. For patients not recognized as being in a palliative phase an individualized well-considered plan of action is missing [11,12].

Several illness trajectories have been described for people with progressive chronic illnesses [13,14]. For none of these trajectories the right moment to start palliative care has been defined yet. Particularly regarding patients with non-malignant diseases, such as advanced chronic obstructive pulmonary disease (COPD) and congestive heart failure (CHF), recognizing or defining the moment when palliative care should be taken in consideration seems difficult (Figure 1) [15,16]. In a national questionnaire among multiple palliative care providers the lack of prognostic indicators and clinical triggers for starting end of life care appeared to be the most important missing link in applying palliative care in primary care [17]. By integrating palliative care into curative care practices or combining palliative care with disease-oriented management earlier in the disease trajectory, chronically ill patients nearing the end of life reported improved satisfaction with care and demonstrated less acute interventions and were more likely to die at home [18,19].

**Figure 1 F1:**
[figure not shown]
**What is the moment to start palliative care?, a modified figure of Lynn and Adamson**[37]
.

The second challenge in bringing the WHO definition into clinical practice, for which early identification is a prerequisite, is a structured proactive palliative care planning. Palliative care programs appeared to reduce symptom distress and improve patient and family satisfaction. Important elements of structured proactive palliative care proved to be coaching the patient to make choices regarding future interventions or restrictions,[20-22] consulting caregivers,[18] eliciting values and addressing the psychological, existential and social context of patient and informal caregiver [23,24]. By proactive planning death at home could be enhanced, [25-27] the number of unforeseen transfers decreased,[28] hospital lengths of stay and aggressive interventions diminished and consequently costs and utilization decreased [28-30].

For GPs a structured proactive palliative care planning is a challenge, as patients with an advanced chronic disease are often under supporting care of the disease-specific specialists until far in the disease trajectory [31]. The GPs should pick up their role as coordinator of palliative care against the mainstream of disease-oriented interventions [32,33]. Several studies concluded that when a GP is part of a team, palliative care improves on different aspects; for patient, informal carer and the participating GP [34,35].

### Aims of the study

#### Research questions

In this study we aim to answer the following questions:

Does early identification and proactive palliative care planning of palliative patients by the GP influence

1. Place of death, number of transitions and number of contacts with the out of hours primary care service?

2. Quality of life of patients and their informal caregivers and prescriptions?

3. GP satisfaction with the delivered palliative care and their own assessment of their ability to provide palliative care?

The objective of this report is to present the study protocol used for the data collection in 2009 and 2010. We describe the protocol of the study, provide a description of the intervention, the methodology and the baseline characteristics of the participating GPs. The described methodology will also serve as a reference for future publications about this study.

## Methods/Design

### Study design

We performed a two-armed randomized controlled trial.

We studied the following hypothesis: H_0_: training GPs in early identification of palliative care patients and proactive care planning will not increase the percentage of patients that die at home, will not reduce the amount of hospital admissions and will not reduce the number of contacts with the out of hours primary care service. This hypothesis will be rejected if the training has a significant positive effect on these aspects of care.

### Power calculation

Sample size was based on number of contacts with the out of hours primary care service. To detect a difference between the intervention and the control group with a power of 80% and an alpha error of 0.05 minimum sample size was 96 patients in both groups when 20% reduction in out of hours contacts was considered.

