### Participants

GPs in two comprehensive cancer centre (IKO and IKZ) regions in the South-East of the Netherlands were invited by mail to participate in the study. After one month a reminder was send to non-responders. Excluded were GPs who are consultant in palliative care or who are locum. GPs that wanted to participate were stratified for degree of urbanization and working hours (part-time or full-time) and were randomized assigned to the intervention or the control condition by an independent statistician. To prevent contamination, those GPs working together in the same practice were placed in the same study group.

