### Data management and plan of statistical analysis

All data were entered in a database and analysed with SPSS 16.0. In both study groups, all patients who died during the inclusion and observation period of the study of a non-acute death, were included in the retrospective analysis. Intervention and control group will be compared on the main outcomes (place of death, number of transitions and out of hours contact, amount of identified patients). Recruitment rates and drop-out rates will be calculated. In case denominators prove to be significantly correlated with the outcome of the main study question, an Anova will be performed to identify potential related or independent factors. Multilevel analysis will be performed.

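### The power statement shows no allowance for practice-level clustering, so 80% power at the 96-patient minimum is not assured

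*Protocol article*

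**What the plan says.** Four places in the protocol article bear on this.

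- **Power calculation.** The driver is a patient-level count: "Sample size was based on number of contacts with the out of hours primary care service". The calculation is made "with a power of 80% and an alpha error of 0.05", and the result is that the "minimum sample size was 96 patients in both groups when 20% reduction in out of hours contacts was considered". The section gives no control rate, standard deviation, test, ICC, cluster size or design effect.
- **Participants.** The GPs who wished to take part "were randomized assigned to the intervention or the control condition by an independent statistician" after stratification, and "those GPs working together in the same practice were placed in the same study group". The practice is therefore the effective unit of allocation.
- **Study design.** The study is described only as a two-armed randomised controlled trial. The word cluster is not used.
- **Data management and plan of statistical analysis.** "Multilevel analysis will be performed". The same section includes every patient with a non-acute death in the period, so 96 is a minimum and not a cap.

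Table 3 (Outcomes section) lists 133 participating GPs: 28 single-handed, 53 in dual practices and 52 in group practices or health centres. It does not say how many practices they represent.

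**The concern.** The allocation and the planned analysis recognise that patients are grouped within practices. The stated sample size gives no sign of it. Patients of one practice share GPs, record-keeping and local out-of-hours arrangements, so their contact counts may be correlated. All of them fall in one arm, so any such correlation inflates the variance of the arm comparison. A multilevel model will reflect this in its standard errors. A patient count that ignores it then corresponds to less power than is claimed.

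The practical stake is how a null result is read. The Weaknesses section already warns that differences may be hard to find. A reader who takes 96 per group as giving 80% power could treat a non-significant result near that number as stronger evidence against a 20% reduction than it is. The article also says that its methodology will serve as the reference for later publications, so the figure is likely to be carried forward.

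**Working it through.** **Inputs from the article.** Power 80%; alpha 0.05; minimum 96 patients, read as per group (192 in all); 133 GPs; practice forms 28 / 53 / 52; palliative patients per GP per year by class (Table 3).

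**Inputs assumed.** Two-sided alpha; ICC 0.05 to 0.10; equal cluster sizes; the number of clusters K, tried at three values:
- K = 133: every GP is a separate cluster.
- K = 72: all partners joined and group practices have three GPs each, 28 + 53/2 + 52/3 = 71.8.
- K = 36: half of those 72 practices return data.

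**Step 1: can 96 be reproduced?** No, because the control value and the standard deviation are missing, and the text does not say whether "when 20% reduction in out of hours contacts was considered" refers to an absolute or a relative reduction. Plain individual-patient formulas do return it for some unstated inputs:
- Two proportions, 55% against 35%: 96 per group.
- Two Poisson rates, control mean 3.7 contacts, relative reduction 20%: (1.960 + 0.842)² x (1.8 x 3.7) / (0.2 x 3.7)² = 95.5, so 96.
- Two means, relative reduction 20%: 95 to 97 if the SD is 0.49 to 0.495 of the mean.

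So 96 is compatible with a calculation without a design effect. That does not prove it was one.

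**Step 2: power at 96 per group, if 96 holds no inflation.** With m = 192/K patients per cluster:

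DE = 1 + (m - 1) x ICC; power = Φ[(1.960 + 0.842)/√DE - 1.960]

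| Clusters K | m | DE (ICC 0.05 / 0.10) | Power at 96 per group | 96 x DE |
|---|---|---|---|---|
| 133 | 1.44 | 1.022 / 1.044 | 79.1% / 78.3% | 99 / 101 |
| 72 | 2.67 | 1.083 / 1.167 | 76.8% / 73.7% | 104 / 112 |
| 36 | 5.33 | 1.217 / 1.433 | 71.9% / 64.8% | 117 / 138 |

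With DE = 1 the formula returns 80%. With m above 1, any positive ICC makes DE exceed 1 and takes power below 80%. At ICC 0.01 and K = 133 the loss is only 0.2 points. Unequal practice sizes would add to it.

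The last column holds m fixed. If the number of practices is fixed instead, extra patients raise m, and n solves n = 96 x [1 + (2n/K - 1) x ICC], that is n = 96(1 - ICC)/(1 - 192 x ICC/K). For K = 72 this gives 91.2/0.8667 = 105.2 and 86.4/0.7333 = 117.8, so 106 / 118 per group. The m in the formula must therefore be the number of deaths per practice at the restated total.

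**Step 3: the number likely to be analysed.** As a rough proxy, Table 3 class values give 10 x 1.5 + 72 x 4 + 43 x 7 + 6 x 10 = 664 palliative patients per year, or 332 per group. With K = 72, m = 664/72 = 9.22 and DE = 1.411 / 1.822. The requirement is 96 x DE = 136 / 175 per group, and 332 exceeds it. Effective n is 332/DE = 235 / 182, and power is Φ[2.802 x √(effective n/96) - 1.960] = 99% / 97%. If half the practices return data (166 per group, same m), effective n is 118 / 91 and power is 87% / 78%.

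**Step 4: the other reading of the total.** If 96 is the total for both groups together, m halves. With K = 72, DE is 1.017 / 1.033 and power 79.4% / 78.7%. The direction is the same and the loss is smaller.

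**The case against.** The strongest reply has four parts.

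- **The method behind 96 is unknown.** The article condenses a fuller protocol, and the number cannot be rebuilt from what is printed. A reader might infer that the authors computed it as though patients had been individually randomised. The text does not establish that, and a small inflation cannot be excluded. This stands, and it is why the point is worded as no visible allowance.
- **The loss may be trivial.** Table 3 gives practice form, not how many partners joined. If few did, there are close to 133 clusters and the loss is under 2 points at these ICCs. This also stands. The size of the shortfall is conditional, although its direction is not.
- **96 is a floor.** A reader might infer that the trial as run is underpowered, or that 80% power was not delivered. The documents do not support either. All eligible non-acute deaths are analysed, and the Table 3 proxy of 332 per group would give 97-99% power with 72 practices. That proxy counts GP-reported palliative patients, not eligible deaths, and the article says that data from non-responding GPs will be absent. It cannot prove adequate power, but it rules out asserting the opposite.
- **Clustering is handled in the analysis.** The allocation is openly described and a multilevel model is planned, so the planned inference is not the problem. This stands, but it leaves the power statement untouched. The article prints a finished number with a power claim, and that claim should match the allocation and analysis described alongside it.

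**Conclusion.** The defect lies in the stated pairing of 96 patients per group with 80% power. Practices are allocated whole and a multilevel analysis is planned, but the number shows no allowance for either. If 96 contains no design effect, power at that minimum falls short of 80% by about 1 to 2 points with 133 clusters, 3 to 6 with about 72 practices and 8 to 15 with about 36.

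These sizes rest on an assumed ICC of 0.05 to 0.10, assumed practice counts, equal cluster sizes, two-sided testing and the per-group reading of 96. None of these is stated in the article. The finding concerns the planning statement and its use as a benchmark, not the realised power of the trial.

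**What to change.** 1. Describe the design as cluster randomised, with the practice as the cluster, and give the number of practices per arm.
2. In the Power calculation, state the control rate, the SD or dispersion, the assumed ICC and the expected number of deaths per practice (m). Then do one of the following: restate the minimum as 96 x [1 + (m - 1) x ICC], with m taken at the restated total; restate the power that 96 per group gives; or show that 96 already includes the inflation.
3. Say explicitly whether 96 is per group or in total.
4. Add the power for the number of deaths actually expected, using the same ICC and allowing for practices that do not return data.

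The cost is wording and one recalculation. Because all eligible deaths are included anyway, no extra enrolment is needed and the planned analysis does not change. The stated power or minimum will look less favourable than it does now.

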### Participants

GPs in two comprehensive cancer centre (IKO and IKZ) regions in the South-East of the Netherlands were invited by mail to participate in the study. After one month a reminder was send to non-responders. Excluded were GPs who are consultant in palliative care or who are locum. GPs that wanted to participate were stratified for degree of urbanization and working hours (part-time or full-time) and were randomized assigned to the intervention or the control condition by an independent statistician. To prevent contamination, those GPs working together in the same practice were placed in the same study group.

### Ethical considerations

The study was conducted after approval of the research ethics committee of the Radboud University Nijmegen Medical Centre in accordance with the Medical Research Involving Human Subjects Acts (WMO). Patient and physician anonymity was guaranteed throughout the registration and data entry process. Patients and their informal caregiver were invited to participate by their GP. If they agreed to participate in the longitudinal study they received a patient information letter and an informed consent form. Trial registration has been obtained. (The Netherlands National Trial Register: NTR2815)

### The intervention

The intervention for the GPs in the experimental condition consisted of three consecutive parts.

Part one consisted of a five-hours training in early identification of palliative patients and proactive care planning. This training was provided by two experienced GPs with a specialization in palliative care and an extended experience in teaching. Early identification was based on two tools, developed in an earlier stage of the project and described elsewhere (submitted). The first tool is a plasticized card (Table 1) with indicators to identify and recognize patients with respectively COPD, CHF and cancer as being in a stage that palliative care should be considered, the so-called 'Radboud Indicators Palliative Care Needs' (RADPAC). GPs were trained in 1) checking actual problems of the patient in a structured way at the moment of identification, 2) considering potential problems that could be expected in the (near) future and 3) foretelling the most likely scenarios on deterioration and death. A previously developed tool (Table 2) could be used as an abstract of the content of the training and could be used to structure the discussion with the patient and their informal caregiver, and to explore their actual en potential problems and needs (Proactive Palliative Care Planning Card (PPCPC)). The aim was a shared proactive policy to deliver specific, proper and individualized palliative care planning.

**Table 1 T1:** The RADboud indicators of PAlliative Care needs (RADPAC)

Congestive Heart Failure	1. The patient has severe limitations, experiences symptoms even while at rest. Mostly bedbound patients. *(NYHA IV)* 2. There were frequent hospital admissions *(> 3 per year)* 3. The patient has frequent exacerbations of severe heart failure *(> 3 per year)* 4. The patient is moderately disabled; dependent. Requires considerable assistance and frequent care *(Karnofsky-score ≤ 50%)* 5. The patient increases in weight what is not responding to increased dose of diuretics 6. A general deterioration of the clinical situation (oedema, orthopnoe, nycturie, dyspnoea) 7. The patient mentions 'end of life approaching'
**Chronic Obstructive Pulmonary Disease**	1. The patient is moderately disabled; dependent. Requires considerable assistance and frequent care *(Karnofsky-score ≤ 50%)* 2. The patient has substantial weight loss (± 10% loss of bodyweight in six months) 3. The presence of congestive heart failure 4. The patient has orthopnoe 5. The patient mentions 'end of life approaching' 6. There are objective signs of serious dyspnoea (decreased dyspnoea d' effort, dyspnoea with speaking, use of respiratory assistant muscles and orthopnoe)

**Cancer**	1. Patient has a primary tumour with a poor prognosis 2. Patient is moderately disabled; dependent. Requires considerable assistance and frequent care *(Karnofsky-score ≤ 50%)* 3. There is a progressive decline in physical functioning 4. The patient is progressively bedridden 5. The patient has a diminished food intake 6. The presence of progressive weight loss 7. The presence of the anorexie-cachexie syndrome (lack of appetite, general weakness, emaciating, muscular atrophy) 8. The patient has a diminished 'drive to live'

**Table 2 T2:** Reminder for proactive planning and disease specific potential problems

Somatic domain		Social en financial domain	
Policy		Policy	

Actual problems:		Actual problems:	

Expected problems: Scenario of dying:		Expected problems:	

**Care provision and activity of daily living**		**Sense of meaning and psychological domain**	

Policy		Policy	

Actual problems:		Actual problems:	

Expected problems:		Expected problems:	

**Possible future problems** Pain, Dyspnoe, Ileus, Delirium, Fear, Depression, Coma, Liver/renal failure Strain of informal caregiver, Special technical care			

**Disease specific interest** CHF: anaemia switch of the defibrillator weight COPD: medicinal/non-medicinal possibilities against dyspnoea			

(Proactive Palliative Care Planning Card, PPCPC)

The second part of the intervention consisted of a coaching session for the GPs with a physician specialized in palliative care regarding each identified patient included in the study. In this session the GP received feedback and suggestions on the proposed proactive palliative care plan, potential future problems and potential scenarios of deterioration and death.

The third part of the intervention consisted of two peer group sessions of the intervention GPs, eight and ten months after the initial training session. In these sessions the main focus was patient-GP communication techniques regarding having the first conversation with the patient about palliative care (and thus about end of life issues). GPs also had the opportunity to exchange experiences on this topic. Data for process description were collected during the first year after T0. Effect evaluation took place in April 2011.

### Control group

GPs in the control group were asked to provide usual care. They were not trained and had no access to RADPAC, nor to the PPCPC. Consultation by telephone with the palliative care helpdesk of the Comprehensive Cancer Centre was possible as usual. This service is available 24/7 for all GPs in the two comprehensive cancer centre regions in the South-East of the Netherlands; mostly these consultations are on problems in the terminal phase for which the GP needs specialised advice for acute problems. For GPs in the control group a training will be organized after the intervention study is closed.

